## Abstract

**Background:**

Optimal management of chronic arthritic pain experienced by older adults involves applying active self-management strategies every day. Cost-effective and innovative strategies to help build older people’s pain self-management capability are required. This study protocol is designed to evaluate the feasibility, acceptability, and preliminary outcomes of a pain self-management app among older people living in the community with arthritic pain.

**Methods/design:**

This is a phase I feasibility study. A pre-post test study design will be used to trial a freely available pain self-management app named Rheumatoid Arthritis Information Support and Education (“RAISE”) for 14 days. Thirty community-dwelling older people living with arthritic pain who use a smartphone will be recruited from (1) various community-based social clubs/organizations/groups or (2) via Facebook groups with potentially high number of older members. In addition, snowballing sampling approach will also be utilized.

These participants will trial the RAISE app, which was selected following a systematic evaluation of all available chronic pain apps by the investigator team. A face-to-face or telephone-based meeting will be organized with all consenting participants in order to seek their informed consent, download and set up the intervention app on their mobile device, be provided with app training, and complete the pre-test data (Time 1 (T1)). Participants will be asked to use the RAISE app as desired for 14 days. Post-test data collection (Time 2 (T2)) will occur on day 15. Data collected includes participant’s demographic and clinical information, pain scores, pain self-efficacy, and online technology self-efficacy. Participants will be invited to take part in a semi-structured telephone interview at T2 to explore their experiences of using the app.

An evaluation of patterns of app use, recruitment, retention, attrition rates, and analysis of the missing data will inform the study and intervention feasibility. Preliminary outcomes are participant’s pain intensity and interference, pain self-efficacy, and online technology self-efficacy.

**Discussion:**

This study will help us better understand the feasibility and acceptability of using this novel intervention among community-dwelling older people living with arthritic pain. The results will also help inform future pain app studies.

**Trial registration:**

Australia New Zealand Clinical Trials Registry: ACTRN12617000921381.

## Background

Unrelieved pain is one of the most common health conditions affecting the majority of older people (those aged over 65 years) [1–3]. Globally, about 70% of older adults suffer from arthritis-related pain [2, 3]. Although the global economic impact of arthritis remains unknown, it is estimated to cost high-income countries between 1–2.5% of their gross national product [4]. As most older people live in the community, self-management strategies are central to improving their unrelieved chronic pain and minimizing the adverse impact of pain on their lives [5, 6]. Active self-management involves (i) medical management (i.e., medication adherence, dietary modification), (ii) behavior modification (i.e., modifying activities of living, physical, and recreational activities), and (iii) managing emotion (i.e., dealing with fear, frustration, and anger) [7]. Building patients’ capacity to self-manage pain is underpinned by effective instruction, education, and support, augmented with regular medical, nursing, and/or allied health follow-up. Self-management strategies are central to maximizing effective coping with pain and minimizing the adverse impact of pain on older people’s lives [5, 6]. While structured pain self-management programs have traditionally been grounded in face-to-face coaching approaches, there has been a growing interest in the use of technology-mediated self-management intervention to promote and support self-management.

Although younger people outnumber older people in terms of technology engagement, the uptake of new technology among older people is increasing rapidly [8]. The proportion of older people using smartphones has more than doubled since 2014 [9], with over 40% of people aged over 65 years now owning a smartphone [10]. A growing proportion of older people regularly use the internet and source online health information [8]. While digital technology uptake among older people of today is increasing and is yet to reach saturation, the next generations of older people (“baby boomers”) who have grown old with digital technology are likely to be even familiar users. Given this reality, there will be more opportunities to use digital technology-facilitated approaches to reach and meet the needs of the world’s rapidly growing and aging population.

Since the introduction of the smartphone in 2007, its subsequent widespread adoption has fueled the development of a range of health-related applications (apps) that can be accessed from these computerized mobile handsets [11]. Smartphone apps use software that interact with users on an individual basis [12]. Health-related apps form a significant proportion of all apps. Although exercise and wellness apps form the major proportion of the health app landscape, self-management apps for chronic conditions, including pain, are growing [13]. There are currently over 350 pain self-management apps offering pain assessment recording, pain information, and pain self-management plans available on the internet, and this number is expected to increase [14, 15]. While several recent systematic reviews have evaluated the quality of currently available pain-related apps [14–17], only one review has examined the quality and usability of arthritic pain self-management apps for older people [13]. This review identified that only 4 of the available 373 pain apps offered pain self-management advice and support in accordance with the Stanford Arthritis Self-Management Program and reflected current arthritic pain management evidence [13].

There is a paucity of pain app evidence that is applicable to older people, with most studies focusing primarily on younger people’s management of their chronic pain [18–20]. The two app-based interventions tested among older people have both focused on areas outside of pain, such as strength training [21] or falls [22]. As older people with chronic pain indicate a willingness to learn and use smartphones and apps for pain self-management [23, 24], the feasibility, acceptability, and effectiveness of using a pain app to help older people better self-manage their arthritic pain warrant further investigation.

## Aim

The aim of this study is to evaluate the feasibility, acceptability, and preliminary outcomes of a pain self-management app among older people living in the community with arthritic pain.

## Method

### Design

This is a phase I feasibility study. Based on the Medical Research Council’s continuum of evidence structure, this study is classed as a phase I study [25, 26]. Studies classed as phase I are designed to improve the understanding of components of an intervention and their interrelationships. Qualitative testing is recommended for use in these studies so as to facilitate the understanding of how the intervention might work [25]. It is, however, important to note that development and evaluation of a complex intervention is not always a sequential or linear process, and these interventions may work best if they are tailored to local settings instead of a uniform/standardized approach [26].

Feasibility studies are used to determine whether an intervention is appropriate for further evaluation [27]. Adhering to the conceptual framework outlined by Eldridge and colleagues [28], this study could be classed under “feasibility studies that are not pilot studies.” Feasibility studies differ from pilot studies as they are carried out before a main study so as to estimate important parameters required to design the main study, whereas a pilot study is a smaller version of the main study carried out to evaluate if all of the components of the main study can work together [29].

### Participants

This study aims to recruit 30 older people living with arthritic pain, who use a smartphone or a tablet device, and who meet the following inclusion criteria:Living in the community;Aged 65 years or over;Presence of arthritic pain for ≥ 3 months (participant reported);Ability to read and write in English;Ownership of a smartphone/tablet-computer;Ability to give written informed consent

Exclusion criteria include the following:Presence of cancer painUnder end-of-life care pathwaysLiving in an institutional home

### Setting and procedure for recruitment

The screening, recruitment, and consenting process for this study will be carried out by one of the investigators (PB). Prospective participants will be sought from various older people’s club/associations/groups, including Facebook groups across Metropolitan and Regional New South Wales (NSW), Australia. This approach of recruitment is considered because many older Australian utilize their free time keeping active and participating in leisure activities by engaging in social clubs [30]. With over 60% of community-dwelling older Australians involved in a social or support group [31], members of older people-specific social clubs and organizations are expected to be a fair representation of the target population of this project.

Each club/association/group will be approached with a written invitation to participate. Utilizing a snowballing sampling approach, club members will be asked if they could provide a referral to any other club/organization/group that could be contacted with an invitation to participate. Interested clubs/organizations/groups will be asked to circulate the study’s poster among their members in paper or electronic form. Groups that meet in person will be offered an on-site presentation to promote the study and share the invitation to participate.

To facilitate online recruitment, a designated study Facebook page will be created. Administrators of interested Facebook-based groups will be asked to upload the study’s poster on the group’s Facebook page on behalf of the investigator team. Utilizing a snowballing sampling approach will enable study participants to share our study invite among their networks and to refer us to any contacts who they think may have interest in participating.

The first contact with potential participants will be made via one of the three following approaches: (i) during the on-site presentation, (face-to-face contact), (ii) when interested participants contact the investigator responding to the recruitment poster (telephone, email, or via Facebook), (or iii) when a face-to-face contact (prospective participant, club member, or study participant) provides a referral to another prospective participant (telephone or email contact).

Each potential participant will be asked the following three questions to assess if they meet the eligibility criteria: (a) Have you experienced arthritic pain for over 3 months? (b) Are you over 65 years of age? (c) Do you live in the community setting (not in an institutional home like residential aged care facility)? Participants answering “Yes” to all of the three questions will be considered eligible to participate in the study. Those meeting the eligibility criteria will be provided with a brief verbal overview of the study including a clear indication that there is no direct incentive to them in participating in this study. This will be followed by the provision of the written Participant Information and Consent Form. Potential participants will be prompted to ask any questions regarding the implications of participation before signing the consent form. After this time point, potential participants will be advised to get in touch with the study team when they are ready to provide their written consent. This could happen on the same meeting session (or day) of information provision, or could be up to 2 weeks before the end of the recruitment period.

### Sample size

As this is a phase I feasibility study, a sample size calculation is not appropriate. However, consistent with other comparable studies [32, 33], *N* = 30 will be the target recruitment figure.

### Intervention

The intervention to be tested in this study is the free, widely available and downloadable pain self-management app named Rheumatoid Arthritis Information Support and Education (“RAISE”) [34]. The selection was made based on our recent systematic review of the quality and older people-specific usability of all available pain apps identified on the web as of 30 May 2016 [13]. The WebMD Pain Coach app [35] generated the highest quality and usability score [35]; however, this app has recently been removed from the public domain. The app scoring the second highest score RAISE [34] will be selected for evaluation in this study. Written permission has been obtained from the developers of the RAISE app for its use in this study.

### The RAISE app

The RAISE app has been designed by the collaborative effort of the Rheumatology Department of St. James Hospital in Ireland and Arthritis Ireland for the self-management of arthritic pain [36]. The features of the RAISE app could be broadly classed as encompassing the following functions:*Assessment and documentation:* The RAISE app offers an option to assess pain in a 0–5 Numeric Rating Scale (NRS) and keeps a time-stamped record of the NRS score. This pain intensity scale can be used as frequently as the user desires. Users can also record their activity level on a 0–5 NRS, and*Pain self-management education:* The RAISE app provides education on a range of different topics relating to pain self-management such as a provision of education on pain/pain self-management processes, medication use, and communication with health professionals and pain-related problem-solving. Information on fatigue, sleep, and the management of distress along with CBT pain management instructions on relaxation, goal-setting, and activity pacing (20–30 min session) are provided. Finally, there are videos of stretching, isotonic and aerobic exercise with warmup and cooldown stages with the duration and frequency of exercise also indicated.

### Intervention delivery

A meeting (face-to-face or via telephone) will be organized with all consenting participants in order to download and set up the RAISE app on the participant’s mobile device, provide participants with app training and brief them to use the app for 14 days, and collect the pre-test data (Time 1 (T1)). Participants will be shown all of the features of the app and then guided to navigate through the features of the app until they are comfortable using it. In addition, participants will be advised to contact one of the investigators if they require any assistance in using the app throughout the 14-day period.

A wireless-enabled device (wireless internet dongle) will be purchased and used for downloading the app to the face-to-face meeting participant’s device so that they do not have to use their mobile phone’s data allowance for the app download. If a face-to-face meeting is not feasible, and the participant is willing and able to use their own wireless or mobile internet for the app download, this session will be carried out over the phone (telemeeting). Participants will be advised to use the RAISE app as desired for the next 14 days. It is important to note that this study is not prescriptive in terms of how often participants will use the app. They receive brief training on how to use the intervention app to ensure they are comfortable with using it; however, the frequency with which they use it is up to them.

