### Study outcomes

For the purpose of this study, following three preliminary outcomes will be measured before and after the intervention: (1) pain severity and interference, (2) pain self-efficacy—described as confidence people with ongoing pain have in performing activities while in pain [37], and (3) online technology self-efficacy—described as confidence in using various kinds of online technology [38]. In addition to these preliminary outcomes, this study will also measure the following feasibility outcomes: (1) recruitment, refusal, and attrition rates; (2) proportion and patterns of missing data; and (3) ability to recruit 30 participants within 6 months of recruitment commencement.

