### Data collection

Data collection will be carried out by one of the investigators who is a registered nurse with a Bachelors of Nursing (Honors) qualification and is currently undertaking a doctoral degree. She has over 5 years experience of working in healthcare research environment across various aged and chronic care trials in the aged care and hospital setting.

Data will be collected using the following questionnaires (refer Table 1):Pain outcomes Case Report Form (CRF)—This CRF includes three valid and reliable outcomes measurement questionnaires, namely the Brief Pain Inventory-short form [39], the short form Pain Self-Efficacy Questionnaire (two-item scale) [40, 41], and the Online Technology Self-Efficacy Questionnaire [38].The Brief Pain Inventory (BPI)-short form—The BPI-sf is a validated, widely used, self-administered questionnaire developed to assess the severity of pain and the impact of pain on daily functions [39].Short form Pain Self-Efficacy Questionnaire (PSEQ-2)—The PSEQ-2 is a valid and reliable two-question tool designed to assess the confidence people with ongoing pain have in performing activities while experiencing unrelieved pain [40, 41]. This tool is deemed to be a robust measure of pain self-efficacy [42].Online Technologies Self-Efficacy Scale (OTSES)—The OTSES is a valid tool that is designed to measure an individual’s self-efficacy in using online technologies [38].Demographic and clinical survey—The survey captures participants’ demographic, social, and health-related information and includes the Charlson Comorbidity Index [43], the Life-Space Assessment questionnaire [44], and the Australian-modified Karnofsky Performance Scale [45].

**Table 1 Tab1:** Data collection tool and time points

Tool	Day 0 (T1)	Day 15 (T2)
Demographic and clinical survey captures the following:	✓	✘
• Participant’s demographic information, medication use details, social support, technology use pattern, and clinician details		
• Comorbidity: Charlson Comorbidity Index		
• Mobility: Life-Space Assessment questionnaire		
• Performance status: Australian-modified Karnofsky Performance Scale		
Pain outcomes measurement Case Report Form includes the following:	✓	✓
• The Brief Pain Inventory-short form		
• Pain Self-Efficacy Questionnaire-short form (two-item scale)		
• Online Technology Self-Efficacy Questionnaire		

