### Statistical analysis

This study will utilize the IBM Statistical Package for Social Science (SPSS) software for management and analysis of data. Descriptive statistics will be used to synthesize the sociodemographic data of the participants. Frequencies and percentages will be reported for categorical variables, normally distributed continuous variables will be presented as mean and standard deviations, and median and interquartile range will be reported for non-normally distributed continuous variables. Participant’s pre-test self-reported pain data (pain intensity and pain interference), pain self-efficacy, and online technology self-efficacy will be compared with their post-test reports.

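### Both accounts of the set-up meeting list the T1 questionnaires after app training, which sits against an outcome baseline taken before the intervention

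*Protocol article*

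**What the plan says.** The set-up meeting is described twice in the protocol article.

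- **Abstract, Methods/design.** After consent is sought, participants are to "download and set up the intervention app on their mobile device, be provided with app training, and complete the pre-test data (Time 1 (T1".
- **Method, Intervention delivery.** After installing the app, the investigator is to "provide participants with app training and brief them to use the app for 14 days, and collect the pre-test data (Time 1 (T1". The section then describes the training: "Participants will be shown all of the features of the app and then guided to navigate through the features of the app", continuing until they feel comfortable with it.

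On timing, Study outcomes states that the "following three preliminary outcomes will be measured before and after the intervention". The three are pain severity and interference, pain self-efficacy, and online technology self-efficacy. Data collection describes the last instrument (OTSES) as measuring "self-efficacy in using online technologies". Table 1 places T1 on Day 0 and T2 on Day 15, with no order within Day 0. Under Statistical analysis, each participant's pre-test values "will be compared with their post-test reports".

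**The concern.** The study has no control arm, so T1 is the only reference value for the outcome estimates. The training is described under Intervention delivery and takes the participant through every feature of the app. According to The RAISE app section, those features include pain education, relaxation and pacing instruction, and exercise videos. One-to-one coaching of this kind is itself exposure to the app, and it could plausibly change how confident someone feels with online technology. If T1 is taken afterwards, it is no longer a clean pre-intervention value. The T1 scores would then describe people who have just been trained, and part of any benefit would be missing from the reported change. That loss cannot be recovered at analysis. The article also says that data collection has already begun.

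**Working it through.** The document gives no effect size, SD or correlation for these outcomes, and its target of 30 is not derived from a calculation. There is therefore no figure of the plan's own to reproduce. The check is first textual, then algebraic, then illustrative.

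**1. Order of tasks, side by side.**

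| Section | Order listed |
|---|---|
| Abstract, Methods/design | consent, install app, training, T1 data |
| Intervention delivery | install app, training and briefing, T1 data |
| Study outcomes | outcomes measured before the intervention and again after it |
| Table 1 | T1 on Day 0, no order within the day |

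The other items stand in working order: consent precedes installation, and installation precedes training. A reader running the meeting from either list would naturally give the questionnaires last. No section places them before the training.

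**2. Effect of that order, if followed.** For one outcome, let Y0 be the score before training, Y1 the score just after training, and Y2 the score at T2.

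- True change over the whole intervention: Δ = Y2 − Y0.
- Immediate training effect: d = Y1 − Y0.
- With T1 taken after training, the observed change is Y2 − Y1 = (Y2 − Y0) − (Y1 − Y0) = Δ − d.

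If d > 0, a gain is understated by d. If only a fraction p of participants complete T1 after training, the mean change is understated by p × d, and the baseline mixes trained and untrained people.

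**3. Which outcomes.**

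- *Online technology self-efficacy:* most exposed, because the training is guided practice with an online technology.
- *Pain self-efficacy:* possibly exposed, because the walk-through shows the pain education content.
- *BPI pain severity and interference:* unlikely to move within one meeting.

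**4. Illustrative scale.** Assumptions, none of them from the document: equal SD at T1 and T2, correlation r between them, all 30 pairs complete, every participant trained before T1, and a training shift d of 0.2 to 0.5 SD.

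SE of mean change = √(2(1 − r)) / √30, in SD units.

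| r | SD of change | SE | 0.2 / SE | 0.5 / SE |
|---|---|---|---|---|
| 0.5 | √1.0 = 1.000 | 0.183 | 1.1 | 2.7 |
| 0.7 | √0.6 = 0.775 | 0.141 | 1.4 | 3.5 |
| 0.8 | √0.4 = 0.632 | 0.115 | 1.7 | 4.3 |

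Under these assumptions the shift is at least about one standard error of the mean change. A smaller d would matter proportionately less.

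**The case against.** The strongest reply is that no sequence is stated. Both sentences list the purposes of one meeting, and no word such as *then* or *after* separates the training from the questionnaires. The label *pre-test* and the Study outcomes section both point to measurement before the intervention. In Intervention delivery, the walk-through is described after the sentence that mentions the T1 data, so text order there is not a firm chronology. This stands: a reader might infer that the baseline is known to be contaminated and the change is biased, but the document does not establish that. The bias is conditional on the order actually used.

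A second reply is that the intervention is the app used for 14 days, so a T1 taken after training but before that use is still a baseline. This is arguable, since the Intervention section names only the app. However, the training sits under Intervention delivery and is itself guided use of the app. If the narrower definition is meant, the article needs to say that T1 is a post-training value.

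A third reply is that running orders belong in a fuller protocol or visit guide. That would answer a complaint of missing detail. Here the article itself lists an order, twice, and that order sits badly with its own statement on timing.

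A fourth reply concerns scale. OTSES covers online technologies in general, so brief coaching on one app may move it little. The shift and the correlation used above have no support in the document. This also stands. A reader might conclude that the whole effect could be hidden, but no total effect is given or assumed, so that does not follow.

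**Conclusion.** The point holds in a conditional form. In both descriptions of the meeting the T1 data come last, after installation and training; nothing places them earlier, and this conflicts with the stated intention to measure before the intervention. If the listed order is followed, the observed change is Δ − d, and a gain in online technology self-efficacy would most plausibly be understated. The effect is less certain for pain self-efficacy and unlikely for the BPI scores.

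The size cannot be determined from the document. The standard errors of 0.12 to 0.18 SD show only that a shift of 0.2 to 0.5 SD, if it occurred, would be visible against sampling error in 30 pairs. They are not evidence that such a shift occurs.

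Severity is moderate to minor. The aim is feasibility and acceptability, the pre-post measures are preliminary, and the article states no hypothesis test or progression rule that rests on them. The harm is to the interpretation of the change estimates, not to error rates. The likely direction is understatement, so this would not by itself produce a false claim of benefit.

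**What to change.** - In the abstract and in Intervention delivery, state that all T1 instruments (BPI-sf, PSEQ-2, OTSES, and the demographic and clinical survey) are completed after consent and before the app is downloaded, demonstrated or taught.
- For participants already enrolled, record the order actually used. If any completed T1 after training, describe their T1 as post-training, and interpret or report their OTSES change, and their PSEQ-2 change, on that footing.
- If T1 after training was intended, say so, and amend the timing statement in Study outcomes to match.

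The cost is a reordering of one existing meeting, one tick-box on the case report form, and two sentences of text. No extra visit or instrument is needed.
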